**２）Secondary Endpoints**

1) Operative time

2) Estimated blood loss

3) Proportion achieving the minimal clinically important difference (MCID) in cervical JOA score recovery rate at postoperative 1 and 2 years

4) Health-related QOL (EQ-5D) at postoperative 1 and 2 years

5) Severity of neck pain, upper limb pain, and upper limb numbness (VAS) at postoperative 1 and 2 years

6) Neck disability index (NDI) at postoperative 1 and 2 years compared to preoperative

7) Retention rate of enlarged lamina at postoperative 1 and 2 years (Retention rate)

8) Percentage of hinge fractures at postoperative 1 and 2 years

9) Percentage of bone union of gutter at postoperative 1 and 2 years

10) Sagittal alignment of cervical spine at postoperative 1 and 2 years (C-SVA, C2-7 angle, T1 slope)

11) Paraspinal muscle cross-sectional area (C4/5 level) at postoperative 1 and 2 years

12) Dural sac cross-sectional area (C3/4, C4/5, C5/6, C6/7 levels) at postoperative 1 and 2 years

13) Grading of the mass posterior to the dural sac at postoperative 1 and 2 years

14) Incremental Cost-Effectiveness Ratio (ICER)

15) Surgical complication incidence

[Rationale]

(1)(2) The Clinical Question (CQ) that led to this study's design is: “While the plate method is a simple surgical technique, it is expensive. Could the less expensive conventional method (suture-anchor) be equally effective and safe compared to the mini-plate?” Since the simplicity of a surgical technique can be measured by operating time and blood loss, these were set as secondary endpoints as direct measures to answer the CQ.

(3) In recent years, evaluating treatment effectiveness has commonly involved not only simple comparisons using patient-reported outcome measures but also assessment via the MCID (Minimal Clinically Important Difference). If treatment yields a change exceeding the MCID threshold, the treatment is considered effective. The MCID for recovery in the JOA score in compressive myelopathy has been reported as 52.8%^19)^. As secondary endpoints, comparisons between treatment groups at 1 and 2 years will be made not only for the direct intergroup comparison of recovery rates but also for the proportion achieving the MCID.

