(4) ～(6)　The JOA score is a physician-led assessment of spinal cord symptoms originating from the cervical spine. Patient-reported outcomes such as EQ-5D, VAS, and NDI were set as secondary endpoints. Furthermore, EQ-5D will also be used as the utility value when calculating the incremental cost-effectiveness ratio.

(7) For safety assessment, the retention rate^7)^ (Figure 4), an objective indicator for enlarged lamina reclosure, was set as a secondary endpoint.

[figure not shown]

(8) As a safety endpoint, the proportion of hinge fractures in enlarged laminar segments on CT^8)^ was set as a secondary endpoint.

(9) As an endpoint for surgical goal achievement, the proportion of hinge fractures showing bone union on CT was set as a secondary endpoint.

(10) Postoperative cervical kyphotic deformity is a morphological change that leads to recurrence of spinal cord symptoms and poor outcomes in cervical laminoplasty^7-9)^. As indicators of kyphotic deformity, the C2-7 lordotic angle and C-SVA were set as secondary endpoints, along with the C7 slope as a factor influencing these (Figure 5).

[figure not shown]

(11) Reduction in the cross-sectional area of the paraspinal muscles (Fig. 6), which are cervical extensors, has been reported as a factor influencing occipital pain^20)^ and as a factor involved in post-laminoplasty reclosure^7)^. Therefore, the postoperative paraspinal muscle area at the C4-5 level was set as a secondary endpoint.

[figure not shown]

(12)(13) Post-laminectomy membrane, caused by posterior dural scarring after laminectomy, is considered a factor in spinal cord re-compression^21)^. However, its incidence rate across different laminoplasty techniques remains unclear. Postoperative dural canal area and the Grading of the mass posterior to the dural sac ^22)^ (Figure 7) were set as secondary endpoints to evaluate spinal cord re-compression.

[figure not shown]

(14) A key objective of this study is to demonstrate that the experimental treatment (suture- anchor) is non-inferior in efficacy and safety to the control treatment (mini-plate), while being less expensive and offering superior cost-effectiveness. As an indicator for comparing the cost-effectiveness between the experimental and control groups, the commonly used measure, ICER, was set as a secondary endpoint.

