Collect direct medical costs at the facility where surgery was performed for each patient at discharge, and at 1 and 2 years post-surgery. Direct medical costs include inpatient treatment costs and outpatient treatment costs for the following services, summing ①, ②, and ③.

① Inpatient treatment costs for DCM surgery (surgery-related costs [surgery, surgical drugs, anesthesia, anesthetic drugs]), excluding surgical fees

② Outpatient costs for DCM after the surgery date (consultations, tests, drugs, other)

③ Rehospitalization costs for adverse events (inpatient treatment fees excluding surgery, surgery-related costs [surgery, surgical drugs, anesthesia, anesthetic drugs])

The cost-effectiveness evaluation metric uses the Incremental Cost-Effectiveness Ratio (ICER). The ICER is calculated by subtracting the control group's costs from the trial treatment group's costs. (ICER). ICER is calculated by dividing the incremental cost—the difference between the trial treatment group's costs and the control group's costs—by the incremental effect—the difference between the trial treatment group's effect and the control group's effect.

The outcome measure used is QALY (quality-adjusted life year). QALY is calculated using a Markov model that accounts for patients requiring reoperation or experiencing death, based on QOL measured by EQ-5D. Utility values and cost values are discounted annually at a rate of 2%, as recommended by the Central Social Insurance Medical Council (https://c2h.niph.go.jp/tools/guideline/guideline_ja.pdf).

(15) Surgical complication incidence

Surgical complications are categorized into intraoperative, early postoperative (within 30 days after surgery completion [wound closure]), and late postoperative (from day 31 after surgery up to 2 years postoperatively) complication rates.

Mortality (all deaths during the study period) and reoperation rate within 2 years postoperatively are recorded independently for complications.

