For FAS subjects, perform analyses similar to those for primary endpoints on the change in each evaluation item from preoperatively to 1 year postoperatively.

Additionally, perform analyses similar to those for secondary endpoint (2) on the change in each evaluation item from preoperatively to 1 and 2 years postoperatively.

(11) Paraspinal muscle cross-sectional area (C4/5 level) at postoperative 1 and 2 years

For FAS, perform the same analysis as for primary endpoints on the change in paraspinal muscle cross-sectional area from preoperatively to 1 year postoperatively.

Additionally, perform the same analysis as for secondary endpoint (2) on the change in paraspinal muscle cross-sectional area from preoperatively to 1 and 2 years postoperatively.

(12) Dural sac cross-sectional area (C3/4, C4/5, C5/6, C6/7 levels) at postoperative 1 and 2 years

For FAS subjects, perform the same analysis as for the primary endpoint on the change in dural canal area from preoperative to 1-year and 2-year postoperative time points.

Additionally, perform the same analysis as for secondary endpoint (2) on the change in dural canal area from preoperative to 1-year and 2-year postoperative time points.

(13) Grading of the mass posterior to the dural sac at postoperative 1 and 2 years

For FAS subjects, classify posterior spinal canal compression at 1 and 2 years postoperatively into mild (Grade 1-3) and severe (Grade 4-5). Calculate the proportion of severe posterior spinal canal compression at 1 and 2 years postoperatively by group. For between-group comparisons, calculate the difference in the proportion for each evaluation item and its 95% confidence interval, then perform Fisher's exact test. Use the Clopper-Pearson method to calculate the confidence interval.

(14) Incremental Cost-Effectiveness Ratio (ICER)

Calculate the ICER of the test treatment group relative to the control group.

Refer to Section 8.1.2 for details on the calculation method.

(15) Surgical complication incidence

For SAS, calculate the number of cases and rates of each complication by the following categories for each assigned group.

・Intraoperative complication rate (from start of surgery to end of surgery (wound closure))

・Early postoperative complication rate (from end of surgery (wound closure) to within 30 days postoperatively)

・Late postoperative complication rate (from postoperative day 31 to within 2 years postoperatively)

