**13.2　Expected Benefits, Burdens, and Harms**

1) Expected Benefits

Participation in this study will not directly benefit the research subjects. The research findings may contribute to future advances in medical care.

2) Expected Disadvantages

Regarding the comparison of technical difficulty between the control treatment (plate method) and the experimental treatment (suture anchor method), no difference is expected when performed by surgeons skilled in spinal surgery. Furthermore, no difference is anticipated in complication rates, safety, or other aspects. Indeed, a meta-analysis of short-term outcomes for plate and suture anchor methods in open laminectomy performed overseas reported no significant difference in operating time, blood loss, or JOA scores23. Therefore, we consider there to be no particular disadvantage associated with participating in this study.

Furthermore, participation in this study requires that a Japanese Spine Society Spine Surgery Instructor be employed at each participating institution. This ensures surgical quality and safety, minimizes risks for research subjects, and enables high-quality clinical research.

3) Expected Burden

The duration of hospitalization, number of visits, number of tests, and time spent on examinations/tests associated with participating in this study are comparable to routine clinical care. Furthermore, research subjects will incur no financial burden from participating in this study (see “15. Matters Concerning Monetary Payments and Compensation”).

4) Measures to Minimize Risk

Since this study enrolls patients who require laminoplasty and were already scheduled for surgery, the likelihood of physical risks exceeding those of routine care due to study participation is considered low. However, throughout the follow-up period, the attending surgeon will closely monitor the subject's condition and strive for early detection of surgical complications and adverse events.

Should complications or adverse events arise due to protocol treatment, responses will be considered on a case-by-case basis. For considerations regarding the protection of research subjects' personal information, refer to “21. Handling of Personal Information, etc.”

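### The ICER is fixed as the cost-effectiveness metric in a trial premised on about equal effect at lower cost, where the ratio alone cannot support superior cost-effectiveness

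*Protocol*

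**What the plan says.** Section 8.2(14) of the protocol fixes the metric ("The cost-effectiveness evaluation metric uses the Incremental Cost-Effectiveness Ratio (ICER") and defines it as a ratio: "ICER is calculated by dividing the incremental cost—the difference between the trial treatment group's costs and the control group's costs—by the incremental effect". Differences are suture-anchor minus mini-plate. The effect is the QALY, based on EQ-5D and calculated with a Markov model that allows for reoperation and death.

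Section 10.5.3(14) adds only this: "Calculate the ICER of the test treatment group relative to the control group". For the method it refers to section 8.1.2, which lists the endpoint by name; the definition is in 8.2(14).

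The aim is in the rationale for item (14) in section 5.1. It is called a key objective to show that the anchor is "non-inferior in efficacy and safety to the control treatment (mini-plate), while being less expensive and offering superior cost-effectiveness".

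The premise of near-equal effect appears in three places:
- The clinical question in section 5.1 is "Could the less expensive conventional method (suture-anchor) be equally effective and safe compared to the mini-plate".
- Section 13.2 says that "no difference is anticipated in complication rates, safety, or other aspects".
- The sample size in section 10.2 is reproduced with a true difference of zero (see the working).

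**The concern.** A ratio of cost difference to effect difference works when the effect difference is clearly away from zero and the new treatment is dearer and better. A smaller ratio is then better value. Here the protocol's premise points to a negative numerator and a denominator close to zero. Two things follow.

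- A small change in the QALY difference across zero flips the ratio between a large negative and a large positive number. If the estimated difference is symmetric about zero, either sign is equally likely, whatever its spread.
- When the anchor is cheaper and slightly less effective, the ratio is the saving per QALY lost. A larger number then favours the anchor, the reverse of the usual reading.

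A favourable result could be read as unfavourable, or the other way round, on an objective that the protocol calls key.

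**Working it through.** **The plan's own sample size, to establish the premise.** Inputs from section 10.2: SD 40, margin 20, one-sided alpha 0.025, power 0.9.
- Normal approximation: n per arm = 2 × (1.960 + 1.2816)² × (40/20)² = 2 × 10.507 × 4 = 84.06, so 85 per arm, 170 in total.
- Noncentral t: 86 per arm (power 0.903), 172 in total, as stated. Then 172/0.8 = 215, or 216 for equal arms.
- Both calculations use a true difference of 0. Using the pilot difference (52.6 - 49.9 = 2.7 points in favour of the anchor) would give 2 × 10.507 × (40/22.7)² = 65.2, so about 66 per arm. The plan therefore assumes equal effect on JOA recovery rate.

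**Cost difference.** Section 3.2 gives material costs of 506,700 yen for plates on three laminae and 138,000 yen for anchors on two. It says that surgical fees are the same.
- As quoted: 138,000 - 506,700 = -368,700 yen.
- Two laminae each, assuming plate cost is proportional: 506,700 × 2/3 = 337,800, and 138,000 - 337,800 = -199,800 yen.

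Other cost items are taken as equal for illustration.

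**The ratio.** ICER = cost difference / QALY difference. The protocol gives no expected QALY difference, so the values below are assumptions.

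| QALY difference | ICER at -368,700 yen | ICER at -199,800 yen |
|---|---|---|
| +0.02 | -18.4 million | -10.0 million |
| -0.02 | +18.4 million | +10.0 million |
| -0.10 | +3.7 million | +2.0 million |

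The first two rows differ by 0.04 QALY and have opposite signs. The third row is worse for the anchor than the second, yet its ratio is one fifth of the size.

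**Net monetary benefit on the same inputs.** INMB = threshold × QALY difference - cost difference. The thresholds are also assumptions. Values are in yen, for the cost difference of -368,700.

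| QALY difference | 3 million/QALY | 5 million/QALY | 10 million/QALY |
|---|---|---|---|
| +0.02 | +428,700 | +468,700 | +568,700 |
| -0.02 | +308,700 | +268,700 | +168,700 |
| -0.10 | +68,700 | -131,300 | -631,300 |

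At 5 million yen, -0.02 favours the anchor and -0.10 favours the plate. Reading any ICER below the threshold as good value gives the wrong answer in both cases: 18.4 million looks poor and 3.7 million looks good.

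With the saving of 199,800 yen, INMB at 5 million is +299,800, +99,800 and -300,200 yen for the same three rows. The values are smaller, but the order still runs in one direction.

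**The case against.** Much can be said for the plan, and it limits the point.

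- **Detail left to the SAP.** Section 10 is stated to be an overview. Intervals, a bootstrap or acceptability curves may be in the SAP, which is not shown. Their absence from the protocol is not a finding. What remains is the metric that the protocol itself fixes.
- **The components must be calculated anyway.** A reader might infer that the trial cannot show which arm is better value. The documents do not support this. The analyst needs both differences before dividing, so the quadrant can be recovered once they are shown. Section 10.5.3(4) also analyses EQ-5D change at 1 year in the same way as the primary endpoint, which gives a between-group utility difference with a 95% confidence interval. That is not a QALY difference, however, and neither section says that the two components are reported or how the ratio is to be read.
- **The near-zero QALY difference is inferred.** Equality is assumed for JOA recovery rate, and non-inferiority within 20 points does not imply equal QALYs. Sections 5.1 and 13.2 make it plausible, no more.
- **The noise cannot be sized from the plan.** A reader might want a standard error from a patient-level QALY SD and 86 per arm. The QALYs come from a Markov model with no stated horizon, so such a figure does not follow from the planned method.
- **The saving of 368,700 yen compares unequal extents.** This stands. On equal extents it is about half, which changes the size but not the reversal.

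**Conclusion.** The point holds in limited form. The metric that the protocol fixes fits its own objective badly. If effects are about equal and the anchor is cheaper, the ICER alone is unstable in sign and size. In the cheaper-but-slightly-worse quadrant it falls as the result gets worse: from +18.4 to +3.7 million yen per QALY as the QALY difference goes from -0.02 to -0.10, or from +10.0 to +2.0 million on equal extents. By itself it therefore cannot support the claim of "while being less expensive and offering superior cost-effectiveness".

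This rests on a QALY difference near zero, inferred from the equal-effect premise, and on material costs standing for the cost difference. The illustrative QALY differences and thresholds are assumptions. The ICER is a secondary endpoint, and the primary non-inferiority conclusion is unaffected. The change is worth making but is not critical.

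**What to change.** Amend sections 8.2(14) and 10.5.3(14) as follows.

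- Report incremental cost and incremental QALY separately, each with its uncertainty, derived in a way consistent with the planned Markov model.
- Judge cost-effectiveness by incremental net monetary benefit (threshold × QALY difference - cost difference) at a threshold named in advance.
- Give the ICER only with its quadrant stated: dominance, or savings per QALY lost.
- Point the cross-reference in 10.5.3(14) to 8.2(14), where the definition is.

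Costs and EQ-5D are already collected, so no new data are needed. The cost is a wording change, some added analysis on the model outputs, and the sponsor's commitment to a threshold before the data are seen.

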**・Intraoperative complication rate**

[Definition]

Report complications occurring from the start of surgery to its completion (wound closure), using the study population as the denominator. As complications of particular focus, extract the complications listed below (Table A) according to the registration items of the Japanese Spine Society Registry (JSSR-DB: https://ssl.jssr.gr.jp/db/) and report their frequency and rates.

When a complication occurs, the following details must be documented in the medical record and case report: complication name, outcome, management approach, severity, relationship to cervical spine surgery, treatment details/date of treatment, and whether hospitalization was prolonged.

Table A: Intraoperative Complications Requiring Special Attention

| **Complication** | **Management** |
| --- | --- |
| Dural tear | Primary repair, fibrin glue, artificial dura, fat grafting, spinal drainage, other |
| Massive bleeding (2000ml or more) | Allogeneic blood transfusion, autologous blood transfusion, intraoperative blood recovery, observation, other |
| Nerve Injury (Spinal Cord)/Nerve Injury (Nerve Root) | Steroid administration, observation, laminectomy, etc., other |
| Major Vessel Injury/Vertebral Artery Injury/Other Arterial Injury | Pressure hemostasis only, suturing by relevant department, specialist (vascular surgery, etc.) intervention, catheter, other |
| Vertebral body injury/Transverse process fracture | Implant addition/replacement, Other |
| Misidentification of level | Surgery performed on incorrect upper vertebra(e), Surgery performed on incorrect lower vertebra(e), Other |
| Change to conventional method | Conventional method (Kirita-Miyazaki method): (Level changed), Laminectomy: (Level changed), Other |

**・Early postoperative complication incidence rate (within 30 days after surgery completion (wound closure))**

[Definition]

Using the analysis population as the denominator, describe complications occurring within 30 days after surgery completion (wound closure). For complications of particular focus, extract those listed in the Japanese Spine Society Registry (JSSR-DB: https://ssl.jssr.gr.jp/db/).

If a complication occurs, document the complication name, outcome, management of the complication, severity, relationship to cervical spine surgery, treatment details/date of treatment, and whether hospitalization was prolonged.

Table B: Early Postoperative Complications Requiring Special Attention (Surgical-Related)

| **Complication** | **Management** |
| --- | --- |
| Vascular Injury (Major Vessel Injury/Vertebral Artery Injury/Other Vascular Injury) | Observation, Management by Relevant Department, Management by Specialist (Vascular Surgery, etc.), Catheterization, Other |
| Epidural hematoma | Laminectomy, hematoma evacuation |
| Neurological Symptoms/Muscle Strength Related (Postoperative Upper Limb Paralysis/Postoperative Lower Limb Paralysis/Postoperative Sensory Nerve Paralysis/Bladder/Rectal Dysfunction/Other Complications) | Observation, reoperation, steroid administration, other drug therapy, other |
| Spinal Support Tissue Injury (Vertebral Body Injury/Transverse Process Fracture) | Implant Addition/Replacement/Other |
| Dural Injury (Cerebrospinal Fluid Leak/Meningitis/Intracranial Lesion [subdural hematoma, etc.]) | Conservative management (observation/spinal drainage), reoperation (additional procedures, dural repair, fibrin glue, artificial dura, fat grafting, spinal drainage), antibiotic administration |
| Fixed Metal-Related (Implant fracture, Implant dislocation, Screw malposition) | Observation, implant replacement, implant addition, other  Surgical Site Infection (Superficial/Deep)  Cleaning, Irrigation, Implant Removal, Other |
| Surgical Site Infection (Superficial/Deep) | Wash-out, Irrigation, Implant Removal, Other |
| Misidentification of Level | Surgery on Upper Vertebrae (Intervertebral Space), Surgery on Lower Vertebrae (Intervertebral Space), Other |
| Other (Postoperative Impairment Due to Positioning), Ocular Impairment [Corneal Injury, etc.], Blindness, Dysphagia, Other | Observation, Additional Surgery |

Table C: Particularly Noteworthy Early Postoperative Complications (Systemic Complications))

| **Complication** | **Management** |
| --- | --- |
| Acute Heart Failure | Observation, Conservative Treatment, Endoscopic Treatment/IVR, etc., Surgical Treatment, Other |
| Myocardial Infarction | Observation, Conservative Treatment, Endoscopic Treatment/IVR, etc., Surgical Treatment, Other |
| Pulmonary infarction | Observation, Conservative Treatment, Endoscopic Treatment/IVR, etc., Surgical Treatment, Other |
| Pulmonary embolism | Observation, Conservative Treatment, Endoscopic Treatment/IVR, etc., Surgical Treatment, Other |
| Peripheral venous thrombosis (symptomatic) | Observation, Conservative Treatment, Endoscopic Treatment/IVR, etc., Surgical Treatment, Other |
| Respiratory Failure | Observation, Conservative Treatment, Endoscopic Treatment/IVR, etc., Surgical Treatment, Other |
| Aspiration Pneumonia | Observation, Conservative Treatment, Endoscopic Treatment/IVR, etc., Surgical Treatment, Other |
| Pneumonia | Observation, Conservative Treatment, Endoscopic Treatment/IVR, etc., Surgical Treatment, Other |
| Atelectasis | Observation, Conservative Treatment, Endoscopic Treatment/IVR, etc., Surgical Treatment, Other |
| Pulmonary Edema | Observation, Conservative Treatment, Endoscopic Treatment/IVR, etc., Surgical Treatment, Other |
| Cerebral Infarction | Observation, Conservative Treatment, Endoscopic Treatment/IVR, etc., Surgical Treatment, Other |
| Postoperative delirium | Observation, Conservative Treatment, Endoscopic Treatment/IVR, etc., Surgical Treatment, Other |
| Dementia | Observation, Conservative Treatment, Endoscopic Treatment/IVR, etc., Surgical Treatment, Other |
| Intestinal obstruction | Observation, Conservative Treatment, Endoscopic Treatment/IVR, etc., Surgical Treatment, Other |
| Pseudomembranous colitis | Observation, Conservative Treatment, Endoscopic Treatment/IVR, etc., Surgical Treatment, Other |
| Gastrointestinal Perforation/Gastric Perforation | Observation, Conservative Treatment, Endoscopic Treatment/IVR, etc., Surgical Treatment, Other |
| Pancreatitis | Observation, Conservative Treatment, Endoscopic Treatment/IVR, etc., Surgical Treatment, Other |
| Hepatitis | Observation, Conservative Treatment, Endoscopic Treatment/IVR, etc., Surgical Treatment, Other |
| Cholangitis | Observation, Conservative Treatment, Endoscopic Treatment/IVR, etc., Surgical Treatment, Other |
| Acute Renal Failure | Observation, Conservative Treatment, Endoscopic Treatment/IVR, etc., Surgical Treatment, Other |
| Urinary Tract Infection | Observation, Conservative Treatment, Endoscopic Treatment/IVR, etc., Surgical Treatment, Other |
| DIC | Observation, Conservative Treatment, Endoscopic Treatment/IVR, etc., Surgical Treatment, Other |
| Sepsis | Observation, Conservative Treatment, Endoscopic Treatment/IVR, etc., Surgical Treatment, Other |
| Fractures Due to Falls During Hospitalization | Observation, Conservative Treatment, Endoscopic Treatment/IVR, etc., Surgical Treatment, Other |
| Other | Observation, Conservative Treatment, Endoscopic Treatment/IVR, etc., Surgical Treatment, Other |

